#### Descriptive Norms

Similarly to several previous studies (e.g., Smith and McSweeney, 2007; Croson et al., 2009; van der Linden, 2011), descriptive norms will be assessed with the following items: “How likely do you think is that people you know would donate to this charity?” (1 – very unlikely; 7 – very likely); “How much do you think an average person doing this survey would donate if they won the gift card?” (1 – nothing; 7 – all of it); “How many of the people you know would donate to this charity?” (1 – none of them; 7 – all of them); “How many of the people doing this survey would donate to this charity?” (1 – none of them; 7 – all of them). In previous studies, the reliability of similar four-item measurements of descriptive norms was found to be *p* = 0.76 (Smith and McSweeney, 2007).

#### Charitable Behavior

Since CB is not a unidimensional construct but can be classified into three main categories - helping a stranger, giving time and giving money (Charities Aid Foundation [CAF], 2017) – in this study we decided to measure CB in two different ways:

##### Time donated

The time participants are willing to donate to our charity will be assessed through participants’ interest to volunteer for the charity. Upon finishing with the questionnaires, participants will be asked the following question: “How interested are you in donating your time to volunteer for the charity?”. The question will be scored on a 7-point Likert scale (1 = not interested, 7 = very interested).

##### Money donated

As a part of the study, we will be giving three €/£50 Amazon gift cards to three random participants. Thus, each participant has an equal chance to win a €/£50 Amazon gift card. The amount of money participants are willing to donate to our partner charity will be operationalised as the amount they are willing to donate if they were to win the Amazon gift card. Therefore, participants will answer the following question: “If you were to win the €/£50 Amazon gift card, how much money out of the 50€/£would you be willing to donate to this charity?” If a participant decides to donate e.g., 20€/£, should he/she actually win the gift card, he/she would receive a 30€/£Amazon gift card, while 20€/£would actually be donated to the charity. All the measurements that will be used in this study are presented in the Appendix B.

### Design and Procedure

The procedures described in this protocol are partly based on several other studies. Specifically, when discussing the (in)congruent calls-to–action, we are following the procedures developed in the Winterich et al. (2012) and Kidwell et al. (2013) studies. Winterich et al. (2012) manipulated the description of the charities to be in line either with individualizing or binding foundations, and measured the intentions to donate a part of an Amazon $50 gift card, should the participant win it. However, unlike Winterich et al. (2012) who manipulated the charity description, we decided to manipulate the calls-to-action which is more in line with Kidwell et al. (2013) study in which they constructed individualizing and binding appeals for recycling.

Although neither of these two studies referred to attitudes and social norms, we nevertheless decided to address them in the protocol, as they seem to be important determinants of CB. Here, we draw on the methodology used in the Smith and McSweeney (2007) and van der Linden (2011) studies, but especially on Croson et al. (2009) study, who presented participants with descriptive information and measured its influence on the perception of social norms. Similarly, we are measuring both social norms and attitudes in order to gain insights not only into whether (in)congruent appeals and normative information influence donations, but also into the mechanisms of that relationship.

In sum, although the current protocol is based on several well-established procedures effectively used in previous studies, by combining them and adding several new features, we believe we managed to create a study protocol capable of yielding rich and comprehensive insights into the relationship between morality, attitudes, norms and CB.

## Stepwise Procedure

This experimental study uses a 3 (morally (in)congruent/neutral calls-to-action) × 2 (presence/absence of social norm) between-subjects design and can be conducted online through a custom developed app or existing survey platform. The study procedure can be split into eight steps. (1) Firstly, participants receive a brief description of the study and its goals (e.g., “we want to explore the relationship between morality and CB and test the effectiveness of appeals to donate”) and are asked to provide informed consent for participation. (2) Secondly, participants complete the MFQ and the Moral Internalization subscale. (3) Thirdly, participants are asked to complete a basic demographic questionnaire. (4) Thereafter, the participants are randomly assigned to one of the two different charity causes and to one of six different experimental conditions. We use random assignment to ensure that samples are similar across conditions in terms of observed and unobserved characteristics. After the experimental exposure, participants are first asked about their attitudes toward charitable behavior and perception of social norms regarding the CB (5) and are then asked to indicate their willingness to donate (a) time and (b) money to the charity they were presented (6). The sequence of presenting the questions to donate time versus money will vary randomly in order to minimize the potential influence of sequence on both donation measures. Next, the participants are provided with a feedback regarding their scores on the MFQ and moral identity internalization questionnaire (7). Finally, an optional step is asking permission to collect participants’ Facebook data. Participants can either accept or deny this request. Regardless of their choice, in the last step, debriefing about the study and contact for further inquiries are provided (8). See Figure 2 for a visualization of this procedure.

**FIGURE 2 F2:**
[figure not shown]
Schematic representation of the stepwise procedure.

## Statistical Analysis

To test for the effects of moral congruence of the calls-to-action, descriptive social norms, and their interaction on donations of time and money, a multivariate analysis of variance (MANOVA) will be conducted. In the same analysis, a test for the moderating effect of moral internalization on the congruence of the calls-to-action will also be conducted. This approach allows researchers to account for potential relationships between our dependent variables, and to test whether the experimental manipulations influence participants on a combination of different types of donations (Field, 2009). Furthermore, in comparison with univariate ANOVA, that requires several individual tests, using MANOVA reduces the probability of making a *Type I* error.

To test whether attitudes toward CB mediate the effects of (in)congruence of the calls-to-action on CB, and whether descriptive social norms mediate the effects of normative information on CB, a mediation analysis will be conducted. This can be done by using the bootstrapping method developed by Preacher and Hayes (Hayes, 2013). This is because previous approaches related to this analysis, such as the causal step approach (Baron and Kenny, 1986), have been criticized for lack of power, the underlying assumptions and inability to directly evaluate potential mediation (MacKinnon et al., 2002).

To determine if people’s moral foundations can be predicted from their Facebook data, various machine learning algorithms can be employed^5^. However, as this part of the study is exploratory and primarily concerned with maximizing prediction accuracy, we cannot specify the exact algorithm which will be reported. Various models and approaches can be tried out, choosing the one that exhibits the least amount of generalization error, i.e., the one that performs best on unseen data, which will be determined through cross-validation. Some possible approaches are LASSO (*Least Absolute Shrinkage and Selection Operator*) regression, multiple linear regression on clustered data and principal component regression^6^ (James et al., 2013; Kosinski et al., 2016).

The analyses can be conducted using the R language (R Core Team, 2017). For implementing the various machine learning algorithms, we will use existing packages, such as glmnet (Friedman et al., 2010), irlba (Baglama et al., 2017) and topicmodels (Grün and Hornik, 2011).

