## Aims and Hypotheses

The project has five aims:

(i)to investigate the effect of morally (in)congruent calls-to-action and salient descriptive social norms on CB;(ii)to explore whether these effects occur when the charity’s cause is not aligned with a person’s moral profile;(iii)to examine whether the effects of (in)congruent calls-to-action are moderated by participants’ moral internalization scores;(iv)to investigate whether attitudes toward CB mediate the effect of (in)congruent calls-to-action on CB and whether descriptive social norms mediate the effect of normative information on CB;(v)to investigate whether individuals’ moral foundations can be predicted based on their Facebook behavior.

In previous studies, calls-to-action congruent with one’s moral foundations increased CB (Winterich et al., 2012). Therefore, we hypothesize that morally congruent calls-to-action will have a greater positive impact on CB compared with morally incongruent and neutral calls-to-action, regardless of whether the charity cause itself is in line with one’s moral foundations. Furthermore, we hypothesize that providing participants with normative information, thus making the descriptive norm salient, will significantly affect CB. Additionally, we expect that the impact of morally congruent calls-to-action will be greater in individuals with high moral internalization compared to individuals with low moral internalization. Also, in line with the assumptions of TPB (Ajzen, 1985, 1991), we expect that the effects of calls-to-action congruence on CB will be mediated by attitudes toward CB, and that the effect of normative information on CB will be mediated by the perception of descriptive social norms. Finally, although this part of the research would be purely exploratory, we expect to be able to predict some of the participants’ moral foundations by his/her Facebook behavior. The proposed effects are shown in the Figure 1.

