## Materials and Equipment

### Participants

The number of participants needed when conducting the study according to this protocol mostly depends on the desired effect size we would like to be able to detect and the statistical power we would like to achieve. For example, using the multivariate analysis of variance, if we would like to achieve a power of at least 1−β = 0.90 to detect small effects (*f*^2^ = 0.02) with the probability of *Type I* error set at α = 0.05, we would need a sample size of *N* = 439 as calculated using *G^∗^Power 3* (Faul et al., 2007). However, given that it is expected that researchers will have to omit some participants whose scores do not meet the criteria for individualizing and binding groupings which will be determined from the data [due to calls-to-action not being (in)congruent enough with their moral views], it would be advisable to further increase the number of participants by 20%. Therefore, the ideal final sample would be around *N* = 527. Of course, if one would, for example, like to study the effects of (in)congruent calls-to-action and norms on donations to two different charity causes separately (e.g., those hypothesized to be more in line with liberals’ and conservatives’ values), one would need to double this number. On the other hand, if one is willing to the accept somewhat lower power of 1−β = 0.80, that is usually accepted in psychological research, one would need the sample size of *N* = 344, or around *N* = 412 if one decides to increase it by 20%.

The recruitment of participants can take place online. For example, in order to obtain a mixture of conservative and liberal participants, the link to the survey can be disseminated through different conservatively and liberally oriented Facebook groups (see Table A1 in Appendix A). Other online platforms where it is relatively easy to approach the users of different ideological positions can be also utilized, such as Reddit, Twitter etc.

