**FIGURE 3 F3:**
[figure not shown]
The expected effects of morally (in)congruent calls-to-action and descriptive norms on different levels of moral identity internalization.

We also expect to find mediating effects of attitudes and descriptive norms on the relationship between (in)congruent calls-to-action and normative messages on the one side and CB on the other. More precisely, we expect that the individualizing/binding calls-to-action will have a positive impact on donation attitudes of those participants who are high on individualizing/binding moral foundations, resulting in their willingness to donate more of their time and money. Since our second charity cause (refugee support) is already supposed to be more appealing for those high on individualizing foundations, we do not expect the individualizing calls-to-action to have a major additional impact on participants’ donating attitudes or behavior. On the other hand, we do expect that the binding calls-to-action will have a bigger impact, shifting the attitudes and increasing CB of those higher on binding moral foundations, since they are expected to have relatively negative attitudes toward such charity. See Figure 4 for a schematic representation of these effects.

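### Charity cause is randomised but absent from the 3 × 2 design label and the MANOVA, so aim (ii) and the hypothesis that congruent calls work whatever the cause have no stated test

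*Protocol article*

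**What the plan says.** - **Design (Stepwise Procedure).** The study is labelled as three call types crossed with "2 (presence/absence of social norm) between-subjects design and can be conducted online". Step 4 of the same section then says "the participants are randomly assigned to one of the two different charity causes and to one of six different experimental conditions". That is 2 × 6 = 12 cells, not six.
- **Aim (ii) (Aims and Hypotheses).** The aim is "to explore whether these effects occur when the charity’s cause is not aligned with a person’s moral profile". The first hypothesis is that congruent calls outperform incongruent and neutral ones "regardless of whether the charity cause itself is in line with one’s moral foundations".
- **Model (Statistical Analysis).** The MANOVA is conducted "To test for the effects of moral congruence of the calls-to-action, descriptive social norms, and their interaction on donations of time and money". One further term is named: "In the same analysis, a test for the moderating effect of moral internalization on the congruence of the calls-to-action will also be conducted". The mediation paragraph does not mention cause either.
- **Sample size (Participants).** N = 439 for 90% power at f² = 0.02 and α = 0.05, raised by 20% to about 527. If a researcher wishes to study the two causes separately, "one would need to double this number".
- **Predictions (Anticipated Results).** Congruent appeals of either frame are expected to yield significantly more charitable behaviour than neutral or incongruent ones. For the refugee charity, after Figure 3, the text says "we do not expect the individualizing calls-to-action to have a major additional impact on participants’ donating attitudes or behavior", and expects a bigger impact of the binding call in those higher on binding foundations.

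**The concern.** The article names its model term by term and gives aims (i), (iii), (iv) and (v) an analysis. Aim (ii) alone has none. Because the factors are listed explicitly, this is not detail left to an unseen analysis plan: a factor that is randomised is left out of the stated model.

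A congruence effect averaged over both causes cannot support a claim that holds for each cause. The average can be positive because of the neutral charity alone. Someone following the plan as written would have to answer aim (ii) with an analysis chosen after seeing the data, although Aims and Hypotheses sets it out in advance and Significance of Research says that the project will contrast appeal and cause explicitly.

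The predictions also pull apart. For a participant high on individualizing foundations who is shown the refugee charity, the general hypothesis says the congruent call beats the neutral one. The later text expects little extra from it. A difference of that kind between causes is what the stated model has no term to detect.

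**Working it through.** **1. Aims against analyses.**

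| Aim | Stated analysis |
|---|---|
| (i) congruence and norm | MANOVA main effects and their interaction |
| (ii) cause not aligned with profile | none |
| (iii) moderation by internalization | congruence × internalization in the same MANOVA |
| (iv) mediation | bootstrap mediation |
| (v) prediction from Facebook data | machine learning with cross-validation |

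**2. Reproducing the plan's N.** Noncentral F for Pillai's trace, with p outcomes, a hypothesis of q df, k cells and s = min(p, q):

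- df1 = p·q; df2 = s(N − k − p + s); λ = N·s·f².
- Inputs from Participants: f² = 0.02, α = 0.05. From the design: p = 2 (time and money).
- With q = 3, k = 6, N = 439: df1 = 6, df2 = 2 × (439 − 6 − 2 + 2) = 866, λ = 439 × 2 × 0.02 = 17.56, power 0.900. For 80% power the same formula gives N = 344.

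Both stated figures reproduce exactly, and do so with k = 12 as well. No single named effect of the 3 × 2 layout has 3 df (congruence 2, norm 1, interaction 2). The plan does not say which test was meant, but the point made here does not depend on it.

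**3. Power of the missing test.** Congruence × cause in the 12-cell design has q = (3 − 1)(2 − 1) = 2, with p = 2, so df1 = 4 and, at N = 439, df2 = 2 × (439 − 12 − 2 + 2) = 854.

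| f² of the interaction | λ at N = 439 | Power at N = 439 | N for 90% |
|---|---|---|---|
| 0.02 (the plan's value) | 17.56 | 0.94 | 388 |
| 0.01 (assumption) | 8.78 | 0.65 | 773 |
| 0.005 (assumption) | 4.39 | 0.35 | 1,543 |

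**4. Power within one cause.** Half of 439 is about 220. With q = 2, p = 2, k = 6: λ = 220 × 2 × 0.02 = 8.8, df2 = 428, power 0.65. With 439 per cause (N doubled), power is 0.94.

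**5. Who can inform aim (ii).** The section on (In)congruent Calls-to-Action describes one of its two example charities as more liberal (refugees) and the other as relatively neutral (children). Clear misalignment therefore arises only for binding-profile participants shown the refugee charity. The share with a binding profile is not given. If it is 50%, about 439 × 0.5 × 0.5 = 110 people qualify; if 30%, about 439 × 0.3 × 0.5 = 66. These are then spread over three calls.

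**The case against.** **Participants already deals with cause.** It discloses that analysing the causes separately needs twice the sample, and the article is a template for other researchers. This stands as far as it goes: N = 527 and the doubled N are consistent with each other. But the remark names no test, makes optional what Aims and Hypotheses lists as an aim, and two separate analyses would not show whether the effect differs between causes.

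**Aim (ii) is worded as exploration.** True, but the accompanying hypothesis is not, and the article attaches the exploratory label to the Facebook part.

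**Omitting a balanced randomised factor does not bias the average effect.** Also true. The cost is some precision and, mainly, the absence of an answer by cause.

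Three stronger readings are tempting and are not supported:

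- *That pooling must dilute the congruence effect.* This needs a zero effect for individualizers shown the refugee charity. The text denies only a major additional impact, and it also predicts a bigger effect of the binding call for binding-profile participants. With equal profiles, zero for the former and a doubled effect for the latter (assumptions), the mean multiplier is (1 + 0 + 1 + 2)/4 = 1.00, so there is no dilution.
- *That the stated N serves pooled effects only.* The congruence × cause test has 94% power at N = 439 if its f² is 0.02.
- *That the predictions flatly contradict each other.* A small positive effect could satisfy both passages, and Figure 4 is not shown. What remains is a tension in wording, sharpened by the expectation of significantly more giving.

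**Conclusion.** The concern holds in this form: cause is randomised, is missing from the design label and from the MANOVA, and leaves aim (ii) and the hypothesis about any cause without a stated test. This follows from the text alone and needs no assumption.

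The power consequences are conditional. At N = 439 the interaction test is well powered (about 94%) if f² = 0.02 and not if f² = 0.01 (about 65%). A within-cause congruence test has about 65% power at f² = 0.02. These figures take the plan's effect-size metric, two outcomes, equal allocation to the causes, and 439 analysable participants after exclusions. The stated sample size itself reproduces and is not in dispute. The refugee-charity predictions should be reconciled, but as a matter of wording.

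**What to change.** 1. Describe the design as 3 × 2 × 2 in the Stepwise Procedure.
2. Add charity cause and congruence × cause to the MANOVA, and name the interaction as the test of whether the congruence effect depends on cause. A non-significant interaction should not by itself be read as support for an effect whatever the cause.
3. Report the congruence contrast, with confidence intervals, within each cause, and for binding-profile participants shown the refugee charity. Limit the aim (ii) claim to that group if the two example charities are used.
4. Reconcile the hypothesis in Aims and Hypotheses and the general prediction in Anticipated Results with the later prediction for the refugee charity, giving one prediction per cause.
5. State in Participants that at N = 439 congruence × cause has about 94% power at f² = 0.02 and about 65% at f² = 0.01, and that within-cause results (about 65% power) are exploratory unless N is doubled (2 × 527 = 1,054).

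Cost: a few degrees of freedom, some rewording of hypotheses, and a narrower claim for aim (ii). No change to randomisation or data collection is needed. A full call × profile × cause model with norm would have 3 × 2 × 2 × 2 = 24 cells, about 18 people each at N = 439, so congruence × cause is the more practical main test.

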### The Determinants of Charitable Behavior

In this protocol, charitable behavior (CB) refers to the measurable actions of supporting a charity through donating money or time. To construct an intervention that influences CB, it is first necessary to identify its potential determinants. CB has often been examined in the context of the Theory of Planned Behavior (TPB; Ajzen, 1985, 1991). In the TPB, the immediate causes of any behavior are (1) intentions to perform that behavior and (2) the actual control one has over performing it. In turn, behavioral intentions result from individuals’ attitudes, social norms and perceived behavioral control. Indeed, some studies found that these TPB variables are good predictors of CB. For example, van der Linden (2011) found that attitudes, perceived behavioral control, past behavior and moral norms significantly predicted charitable giving intentions. Smith and McSweeney (2007) reported similar results, but identified injunctive norms as an additional predictor of charitable giving intentions. Thus, one way to increase CB is to influence one or more of its immediate causes, such as changing attitudes and referencing a social norm.

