### Significance of Research

We believe that the current project makes an important contribution both in theoretical and in practical terms. In theoretical terms, we hope to expand the knowledge about the scope of morally (in)congruent appeals. Rare previous research did examine the effects of the congruence between both the appeals and individual’s morality, as well as charity causes and individual’s morality. However, within the current project, we plan to explicitly contrast these two. We aim to explore whether the appeals tailored in line with one’s morality can enhance one’s donations to charitable causes, even in the case of charities for which there is no original affinity. This way, we contribute to the theoretical considerations of the role of morality in CB, but also sketch potential fundraising strategies for charities with different causes. Furthermore, another significant theoretical contribution of this project is the investigation of the role of attitudes in CB change. Specifically, within this project we not only want to show that congruent calls-to-action can have a positive impact on CB, but also to elucidate the mechanism through which this effect operates (i.e., by affecting attitudes toward CB).

Besides the effect of congruent appeals on attitudes and CB, within this project we will investigate the role of descriptive social norms in CB. Specifically, we want to test potential boundary conditions for the effectiveness of descriptive norms, especially related to their saliency. However, here we also want to go a step further and show that, if salient normative information indeed can affect CB, it probably does so through changing one’s perceptions about descriptive norms related to CB. Therefore, we believe that the current project contributes to the theoretical knowledge in several important ways.

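### The bootstrap mediation test cannot separate a mediator that causes giving from one that only correlates with it, yet a positive result is to be read as the mechanism

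*Protocol article*

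**What the plan says.** Aim (iv) in Aims and Hypotheses is "to investigate whether attitudes toward CB mediate the effect of (in)congruent calls-to-action on CB", with the parallel question for perceived descriptive norms and the norm message. Only the Facebook prediction is called exploratory, so mediation belongs to the confirmatory part.

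On method, the Statistical Analysis section names both mediators in one sentence, which ends: "whether descriptive social norms mediate the effects of normative information on CB, a mediation analysis will be conducted". It then says "This can be done by using the bootstrapping method developed by Preacher and Hayes". It prefers this because older approaches were "criticized for lack of power, the underlying assumptions and inability to directly evaluate potential mediation".

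The Stepwise Procedure randomises the charity cause and the six message conditions. After exposure, "participants are first asked about their attitudes toward charitable behavior and perception of social norms regarding the CB", and the questions on donating time and money follow directly. The Moral Foundations Questionnaire (MFQ), moral internalization and demographics are completed before exposure. The Normative Information section lists ideology and previous donations among the demographics. None of these variables is given a role in the mediation analysis.

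On interpretation, Significance of Research sets out "to elucidate the mechanism through which this effect operates (i.e., by affecting attitudes toward CB"). For norms it is more guarded: if the norm message affects giving, it probably works through perceived norms. The Limitations section covers hypothetical bias, grouping and the Facebook app. It does not mention confounding of the mediator-to-giving path.

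**The concern.** An indirect effect is the product of two slopes: message to mediator (a), and mediator to giving within message arms (b). Randomisation protects a and the total effect of the message. It does not protect b, because nobody is randomised to an attitude or a perceived norm. If some trait raises both the mediator and giving, b is non-zero even when changing the mediator would change nothing. The bootstrap reproduces that correlation in every resample. The reasons given for choosing it do not address this, since it relies on the same no-confounding assumption for b.

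Shared causes are plausible on the protocol's own account. The section on changing attitudes reports that moral identity is related to donation intentions, actual donations and donation-related emotions. The attitude scale asks, among other things, whether donating would be pleasant and satisfying.

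At stake is the conclusion on aim (iv) and the theoretical contribution built on it. A charity or a later study could set out to change attitudes or perceived norms on evidence that shows only that they move with the message and correlate with giving.

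**Working it through.** **The plan's own figure.** The protocol gives no error rate or power for mediation. Its MANOVA sample size reproduces with Pillai's trace, using two outcomes, three predictor degrees of freedom and six groups (settings inferred). Then df1 = 6, df2 = 2(N − 6), and λ = N × 2 × 0.02. At N = 439, λ = 17.56 and power reaches 90%; at N = 344, λ = 13.76 and power reaches 80%. Both match the Participants section.

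**Inputs for the mediation check.**
- N = 439 and α = 0.05, from Participants. A two-sided 95% bootstrap interval is assumed.
- Mediator shift a = 0.28 to 0.46 SD. This is an assumption. It borrows the effect range that Significance of Research quotes for intentions and donations; the documents give no figure for the mediators.
- Within-arm correlation ρ between mediator and giving = 0, 0.1, 0.2. This is also an assumption.
- True effect of mediator on giving = 0.

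**Model.** M = aX + e1 and Y = c′X + 0·M + e2, with unit variances and corr(e1, e2) = ρ. X is split about 1:1 (219/220), as for the norm message. The fitted b then tends to ρ and the fitted indirect effect to a × ρ, although the true value is 0. For example, 0.28 × 0.1 = 0.028 SD and 0.46 × 0.2 = 0.092 SD.

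**Approximate rejection rate.** The interval excludes zero about as often as both slopes are significant, so rate ≈ power(a) × power(b).
- Path a: noncentrality a × √(219 × 220/439) = a × 10.48. This gives 2.93 (power 0.83) at a = 0.28 and 4.82 (power 0.998) at a = 0.46.
- Path b: noncentrality ρ/√(1 − ρ²) × √436. This gives 2.10 (power 0.55) at ρ = 0.1 and 4.26 (power 0.99) at ρ = 0.2.

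| ρ | a = 0.28 | a = 0.46 | Simulated range (percentile bootstrap) |
|---|---|---|---|
| 0 | – | – | about 5% |
| 0.1 | 0.83 × 0.55 = 46% | 0.998 × 0.55 = 55% | roughly 42–58% |
| 0.2 | 0.83 × 0.99 = 82% | 0.998 × 0.99 = 99% | roughly 81–99% |

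The rate is not always this high: at a = 0.20 and ρ = 0.1 it is 26%. If the message does not move the mediator at all, it stays at or below about 5%.

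**Requiring a total effect first.** Suppose the message has a real direct effect of d = 0.28, none of it through the mediator. The power of the total-effect test is then about 0.83. Multiplying as if the tests were independent gives 0.46 × 0.83 = 38% and 0.55 × 0.83 = 46% at ρ = 0.1, and 0.82 × 0.83 = 68% and 0.99 × 0.83 = 82% at ρ = 0.2. Simulation of both results together gives about 39–48% and 66–84%.

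**Does baseline adjustment suffice?** At N = 439 and ρ = 0.3, for a = 0.20 / 0.28 / 0.58, simulated false mediation is:
- no adjustment: 56% / 85% / 100%
- covariates carrying half of the common cause: 62% / 85% / 96%
- covariates carrying 80% of it: 25% / 33% / 37%
- covariates carrying all of it: 3% / 4% / 7%

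**The case against.** The strongest reply is that this is the standard caveat on any measured mediator, and that covariates and sensitivity analyses are details an article leaves to the full plan. That is fair for the model specification, and their absence alone would be no finding. But this article itself fixes the type of test, the argument for it and the mechanism reading, and those three do not fit together.

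A second reply is that the mechanism claim presupposes that the message affects giving. With no total effect at ρ = 0.3, the total-effect test rejects in only about 5–8% of runs, while mediation is declared in 56–100%. So the false-mediation rates overstate the risk of a full mechanism claim in that setting. The point stands, but it does not remove the problem: the mediation test is not made conditional on a total effect, and with a real direct effect the joint rates above remain high. The hedge on norms also deserves credit; the attitude statement carries no such hedge.

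Three further points stand. The documents give neither the correlation nor the mediator shift. The protocol does not say that each mediator gets its own model: it speaks of one mediation analysis. And the message-to-norm path is not built in, because two of the four norm items ask about people the participant knows, while the message refers to similar studies.

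**Conclusion.** The point holds. The planned analysis cannot distinguish a causal mediator from a correlated one, and the protocol attaches a mechanism conclusion to it. With no true mediator effect, N = 439 and shifts of 0.28 to 0.46 SD, false mediation runs at roughly 42–58% for a residual correlation of 0.1 and 81–99% for 0.2, against about 5% for none. Both the shifts and the correlations are assumptions. The randomised comparison of messages, the MANOVA and the sample size are untouched.

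Three stronger readings are not supported:
- A reader might infer that the test rejects whenever the message moves a correlated mediator. It does so with a probability that depends on both paths, and at a weak correlation or a small shift the rate is well below certainty.
- A reader might infer that separate one-mediator models are fixed, so that one mediator is credited with the other's effect. The text leaves open whether they share a model.
- A reader might take the statement that "attitudes, perceived behavioral control, past behavior and moral norms significantly predicted charitable giving intentions" as evidence of common causes. It lists predictors of intentions in a cited study, one of them the mediator itself, and does not show confounding.

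**What to change.** In Statistical Analysis:
- State one mediation model with both randomised factors (call-to-action and norm message) and both mediators (attitude and perceived norm).
- Adjust the mediator and outcome equations for the pre-exposure variables already collected: previous donations, moral internalization, MFQ scores and ideology.
- For each indirect effect, report the residual mediator-outcome correlation at which it falls to zero. Do not set a pass threshold, since any fixed value would be arbitrary.

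In Significance of Research and Limitations, say that mediation results are consistent with the proposed mechanism under the assumption of no unmeasured mediator-outcome confounding.

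The cost is a little more analysis work, possibly wider intervals and a more guarded conclusion on aim (iv). No new data or participants are needed. Baseline adjustment reduces the bias but does not remove it unless every common cause is captured, so the sensitivity analysis is needed as well.
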